### **1.2. Baseline knowledge, attitudes and practices (KAP) survey of female and male clients**

Also during this three-month period, a convenience sample of approximately 28 female patients and 28 male patients will be recruited from each of the 18 sites (N=488 female and 488 male patients) to complete a questionnaire regarding knowledge, attitudes and practices (KAP) related to family planning. The purpose of the KAP survey is both to 1) measure the satisfaction with the family planning services offered at the HIV care and treatment clinic, 2) provide information that will be used to design the family planning integration intervention and improve family planning provision, and 3) provide a baseline measure of KAP that will be compared to follow-up surveys at the end of the study.

The survey will be administered face-to-face by an interviewer in the respondent's preferred language in a private area of the centre.

The inclusion criteria for the client KAP survey will be:

- 1) HIV-positive woman or man obtaining care at the FACES site
- 2) Not currently pregnant (if female)
- 3) Age 18 to 45 years old if female; age 18+ if male
- 4) Willing and able to give informed consent

Clients will be excluded if they do not meet the inclusion criteria listed above. Some of the topics included in the KAP survey will be: familiarity with contraceptive methods; prior and current contraceptive use; partner's role in contraceptive decision-making; interest in preventing pregnancy in the future; and acceptability of and satisfaction with currently-offered family planning services at the site. The survey will be adapted from the Demographic and Health Survey modules on contraception, marriage and sexuality, and fertility preferences (see Appendix B1-1 for women's survey and Appendix B1-2 for men's survey). We will train our interviewers to provide referrals for women who need counseling or support services to a local women's non-governmental organization (NGO) working in Migori District, the Women's Action Forum for Networking (WAFNET). These referrals will be provided to women who report domestic abuse (psychological, physical, or sexual) or other negative events during the interviews. Participants will be reimbursed a maximum of USD\$3 (approximately 200 Kenyan Shillings at current exchange rate) for transport.

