  - a. The primary outcome upon which we based our sample size calculation is contraceptive prevalence. According to the 2003 Kenya Demographic and Health Survey, approximately 22% of women in a union in Nyanza Province use a modern contraceptive method. This level of contraceptive prevalence is similar to that seen among clients at the FACES sites. We would like to be able to detect a 8% rise in contraceptive prevalence to 30%.
- 3. Assumptions
  - a. Two-sided alpha of 0.05
  - b. Power of 0.8
  - c. Intra-cluster Correlation Coefficient of 0.01
- 4. Sample size.
  - a. Using these estimates, the needed sample size is approximately 140 women at each of the 18 sites, for a total sample of 2,520 women.
  - b. We plan to initially recruit a similar number, 2,520, of male clients, however our primary outcome for men will be the proportion of male clients who report they or their partner are interested in starting a new FP method after receiving FP counseling during their visit. In order to accurately calculate this sample size, baseline data is needed to estimate the baseline proportion of male clients who would express interest in starting a new FP method. Thus, after the baseline data collection phase a more accurate sample size for male clients will be calculated.

**KAP surveys.** Because the largest sample sizes are required for expected proportions nearer to 0.5 than to 0 or 1, we will take the worst-case scenario and assume that for each individual question on the survey approximately half of the participants will answer correctly. We hypothesize that people in the intervention sites will be more knowledgeable after the intervention at the end of the study, so we would like to test for at least a ten percentage point difference in correct answers among patients in the intervention sites (~60% correct) compared to patients in the comparison sites (~50% correct), as well as a 10% increase in correct answers among patients in the intervention sites compared to the baseline results. For a one-sided test of two proportions using two samples, power of 0.8, and an alpha level of 0.05, the required sample size is 325 patients from the intervention sites and 163 patients from the comparison sites for both men (N=488) and women (N=488).

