### **Data analysis plan**

Analyses of data from the study health facilities, given the randomized cluster design, will mainly be conducted at the cluster (health facility) level. Individual level analyses will take into account

cluster effects. Primary analyses will be based on the “intention to treat” (ITT) principle, with facilities randomized to the intervention group classified as delivering “integrated services” regardless of whether or not individual women actually received integrated services.

Preliminary analyses will be conducted to compute study outcome variables and to summarize characteristics of control and treatment sites to assess the effectiveness of randomization. Initial analyses also will involve inspection of the frequency distributions of variables to identify outlying or unusual values. Following univariate descriptions of the data, bivariate and multivariate associations will be assessed as described below.

Analysis of the primary outcomes, contraceptive prevalence and unintended pregnancy rates, and the secondary outcomes, acceptability of services and knowledge related to contraception, will be based on a comparison of means or proportions between study arms using a weighted t-test that accounts for correlations between individual outcomes within sites. Even though there are only 12 health facilities in the intervention arm and 6 health facilities in the comparison arm, each mean or percentage will be based on a relatively large number of women, and the normal approximation to the binomial distribution can be used. These tests will be evaluated based on a two-sided alternative hypothesis, 80% power, and a 5% type I error rate. The same basic approach will be used for the other primary and secondary outcomes. Results will be summarized as odds ratios for models based on binary responses (e.g. use of contraception or experiencing unintended pregnancy), and mean changes for continuous responses (e.g. score on knowledge test).

As noted above, All open-ended interviews will be tape recorded (if the woman gives informed consent), transcribed, translated to English. A content analysis will be performed using the qualitative software ATLAS.ti in order to describe themes in women’s experiences undergoing contraceptive counseling, receiving family planning methods and in the acceptability of these services.

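### The KAP survey size of 325 + 163 does not give 80% power for the between-arm comparison: about 68% on its own one-sided basis, and 56% or less under the two-sided, clustered analysis that the protocol plans

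*Protocol*

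**What the plan says.** The KAP paragraph of Sample size considerations takes 50% correct as the least favourable case for any single question. It aims to detect a ten-point difference in two contrasts: intervention against comparison sites (about 60% against about 50%), and end of study against baseline within intervention sites. The basis is "For a one-sided test of two proportions using two samples, power of 0.8, and an alpha level of 0.05", and the conclusion is that "the required sample size is 325 patients from the intervention sites and 163 patients from the comparison sites", giving 488 women and 488 men. No intra-cluster correlation or design effect enters this paragraph.

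Section 1.2 says that "a convenience sample of approximately 28 female patients and 28 male patients will be recruited from each of the 18 sites", and section 3.2 repeats this for the end-of-study survey.

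The Data analysis plan names knowledge and acceptability among the outcomes to be compared between arms "using a weighted t-test that accounts for correlations between individual outcomes within sites". It then adds: "These tests will be evaluated based on a two-sided alternative hypothesis, 80% power, and a 5% type I error rate". Under Endpoints, the between-arm contrast is item (c) of secondary outcomes 1 (client knowledge) and 3 (acceptability); the pre/post contrast within intervention sites is item (a) of each.

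**The concern.** There are two separate problems. First, the stated numbers do not agree with each other: 325 + 163 at roughly 2:1 is presented as giving 80% power on the stated one-sided inputs, and for the between-arm contrast it does not. Second, the sizing and the analysis disagree for the same outcomes. One section is one-sided and treats respondents as independent; the other is two-sided and allows for correlation within sites, yet claims the same power.

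The between-arm contrast is the randomised evidence on client knowledge and acceptability. Under Expected Application of Results, rollout depends in part on the intervention appearing acceptable. If a non-significant result is set against a nominal 80% power, it will carry more weight than this survey can give it.

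**Working it through.** **Inputs from the protocol.** Comparison sites p0 = 0.50, intervention sites p1 = 0.60, alpha 0.05 one-sided, power 0.80, sizes 163 and 325 (Sample size considerations, KAP surveys). Two-sided 5% test allowing for clustering (Data analysis plan). 18 sites, so 488/18 = 27.1 respondents per sex per site.

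**Assumption.** The protocol gives no ICC for KAP items. The 0.01 stated for contraceptive prevalence is borrowed, with a range of 0.005 to 0.05.

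**Step 1: reproduce the 325.** With k intervention clients per control client and p̄ = (p0 + k·p1)/(1 + k), the control-arm size is

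n = [z_α·√((1 + 1/k)·p̄(1 − p̄)) + z_β·√(p0(1 − p0) + p1(1 − p1)/k)]² / (p1 − p0)²

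and the continuity-corrected size is (n/4)·[1 + √(1 + 2(k + 1)/(n·k·|p1 − p0|))]². One-sided z_α = 1.645 and z_β = 0.842.

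- k = 1: p̄ = 0.55, n = 305; corrected 324.7, so 325 **per arm**. This matches the stated 325.
- k = 2: p̄ = 0.567, n = 229 control + 458 intervention = 687; corrected 243 + 486 = 729.

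No variant tried (pooled, unpooled or arcsine; corrected or not) gave 325 + 163 at 2:1.

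**Step 2: one-sided power at 163 against 325, no clustering.**

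- p̄ = (163 × 0.5 + 325 × 0.6)/488 = 0.5666
- SE under the null = √(0.5666 × 0.4334 × (1/163 + 1/325)) = 0.0476
- SE under the alternative = √(0.25/163 + 0.24/325) = 0.0477
- Power = Φ((0.10 − 1.645 × 0.0476)/0.0477) = Φ(0.457) = 67.6%

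With the continuity correction the difference becomes 0.10 − ½(1/163 + 1/325) = 0.0954, and power is Φ(0.360) = 64.1%.

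**Step 3: two-sided, no clustering.** Φ((0.10 − 1.960 × 0.0476)/0.0477) = Φ(0.142) = 55.7%. This step needs no ICC.

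**Step 4: two-sided with clustering.** Design effect DE = 1 + (27.1 − 1) × ICC; both standard errors are multiplied by √DE. The detectable difference is the value, from a 50% control rate, at which two-sided power is 80%.

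| ICC (assumed) | DE | Power for 10 points | Detectable difference |
|---|---|---|---|
| 0 | 1.00 | 55.7% | about 13 points |
| 0.005 | 1.13 | 50.7% | about 14 points |
| 0.01 | 1.26 | 46.5% | about 15 points |
| 0.02 | 1.52 | 39.9% | about 16 points |
| 0.05 | 2.31 | 28.3% | about 20 points |

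Rounding up to 28 per site (168 + 336, DE 1.27) gives 47.4% at ICC 0.01. These figures use the normal approximation, which the Data analysis plan allows. A t-test on 16 degrees of freedom gives 41.9% at ICC 0.01, and a cluster-level simulation gives 42.6%.

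**Step 5: pre/post within intervention sites, 325 against 325, no clustering.** One-sided 82.2% (80.0% corrected); two-sided 72.8%.

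**The case against.** The best defence is that the same paragraph sizes two contrasts. For baseline against end of study within intervention sites, 325 against 325 is the right number on the stated one-sided basis before clustering. That stands, and it confines the one-sided arithmetic error to the between-arm contrast. It does not rescue the paragraph, which presents 325 + 163 as sufficient for both contrasts, and the pre/post figure also falls below 80% once the test is two-sided.

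Some stronger readings are not supported.

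- A reader might infer that an equal-allocation result was computed and the control arm then halved. That fits the numbers, but so does taking about 486 to 488, the larger arm of a corrected 2:1 calculation, as a total and splitting it 2:1. The protocol does not say which, and the shortfall is the same.
- A reader might take 47% as the power of the protocol's own analysis. It rests on an ICC stated for a different outcome; the 68% and 56% do not.
- All these figures are for one yes/no item at the deliberately least favourable rate. The Data analysis plan also foresees a continuous knowledge score, which may well have better power, so they are not shown to apply to the knowledge outcome as a whole.
- A reader might extend the point to feasibility. Under Endpoints, that outcome comes from clinic-staff surveys, which this calculation does not size.
- The trial's primary sample size is a separate calculation with a two-sided alpha and an ICC, and nothing here bears on it.

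**Conclusion.** The point holds for the between-arm KAP comparison. On the protocol's own one-sided inputs, 163 against 325 gives about 68% single-item power (64% with the correction that reproduces the 325), not 80%. On the two-sided basis of the Data analysis plan it is about 56% even with no clustering. With clustering it is lower: about 47% if ICC 0.01 carries over to KAP items, and 51% to 28% across ICCs of 0.005 to 0.05. The two sections also contradict each other on sidedness and clustering for the same outcomes, whatever ICC is chosen.

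This should be fixed, but it is not critical: the outcomes are secondary, the respondents are a convenience sample, and the remedy is a matter of wording.

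**What to change.** Keep 488 clients per sex and rewrite the KAP paragraph:

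- Replace the one-sided, independent-respondent basis with the two-sided, clustered, 2:1 basis of the Data analysis plan.
- For the between-arm contrast, state the difference detectable with 80% power: about 13 points without clustering and about 15 at an assumed ICC of 0.01, with 16 at 0.02 and 20 at 0.05 as sensitivity. Equivalently, state about 47% power for 10 points at ICC 0.01. Label the ICC as an assumption for these outcomes.
- State the pre/post contrast within intervention sites separately: about 73% two-sided for 10 points before clustering, with its own allowance for clustering.
- In the Data analysis plan, remove the 80% power claim for knowledge and acceptability.

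The cost is one reworded paragraph, one edited sentence and a less favourable stated figure. No respondents, sites or visits are added. Restoring 80% power for 10 points would be a different matter: with the 18 sites fixed and ICC 0.01, it would take about 93 respondents per site, or 558 + 1,116 = 1,674 per sex. Restating the detectable difference is therefore the proportionate course.

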### **Data analysis plan**

Analyses of data from the study health facilities, given the randomized cluster design, will mainly be conducted at the cluster (health facility) level. Individual level analyses will take into account

cluster effects. Primary analyses will be based on the “intention to treat” (ITT) principle, with facilities randomized to the intervention group classified as delivering “integrated services” regardless of whether or not individual women actually received integrated services.

Preliminary analyses will be conducted to compute study outcome variables and to summarize characteristics of control and treatment sites to assess the effectiveness of randomization. Initial analyses also will involve inspection of the frequency distributions of variables to identify outlying or unusual values. Following univariate descriptions of the data, bivariate and multivariate associations will be assessed as described below.

Analysis of the primary outcomes, contraceptive prevalence and unintended pregnancy rates, and the secondary outcomes, acceptability of services and knowledge related to contraception, will be based on a comparison of means or proportions between study arms using a weighted t-test that accounts for correlations between individual outcomes within sites. Even though there are only 12 health facilities in the intervention arm and 6 health facilities in the comparison arm, each mean or percentage will be based on a relatively large number of women, and the normal approximation to the binomial distribution can be used. These tests will be evaluated based on a two-sided alternative hypothesis, 80% power, and a 5% type I error rate. The same basic approach will be used for the other primary and secondary outcomes. Results will be summarized as odds ratios for models based on binary responses (e.g. use of contraception or experiencing unintended pregnancy), and mean changes for continuous responses (e.g. score on knowledge test).

As noted above, All open-ended interviews will be tape recorded (if the woman gives informed consent), transcribed, translated to English. A content analysis will be performed using the qualitative software ATLAS.ti in order to describe themes in women’s experiences undergoing contraceptive counseling, receiving family planning methods and in the acceptability of these services.

The ACLUSTER software program (Version 2.0) for the Design and Analysis of Cluster Randomized Trials developed by UNDP/UNFPA/WHO/ World Bank Special Programme of Research, Development and Training in Human Reproduction of the World Health Organization, as well as the SPSS statistical software package will be used for analyses. For qualitative data, the ATLAS.Ti software program will be used to code and perform content analysis of the open-ended interviews. A detailed analysis plan will be prepared in the beginning of the study period.

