## **STATISTICAL/ANALYSIS PLAN**

### **Sample size considerations**

**Data abstracted from clinical encounter forms.** We have used ACLUSTER program to generate the number of PSC pairs (or clusters) that we will need to assess changes in contraceptive prevalence and unintended pregnancy. The first input into this program is the size of each cluster (or the number of eligible subjects available at each PSC site). There are a total of 36 FACES-supported PSC sites in Migori, Rongo, Kisumu East and Suba Districts, which are not all equal in size. The first calculation takes into account how we determine the average number of non-pregnant females of reproductive age that are potentially recruitable at each site. The other main input is the desired effect size we aim to be able to measure. Additional inputs include alpha, power and the Intra-cluster Correlation Coefficient (a measure of how similar we expect the two sites in each paired cluster to be to each other, for which we selected an intermediate value). Based on this we need 18 sites, 12 with the intervention and 6 control to be able to evaluate the integration model we propose as described in more detail below.

For the main cluster-randomized trial, the following data were inputted into the ACLUSTER program to generate an estimated number of clusters needed:

- 1. Number of subjects per cluster or site
  - a. The eligible sample includes all FACES-supported PSCs in Suba, Kisumu East, Rongo and Migori Districts. The enrollment in December 2007 at the 16 FACES-supported sites in Suba District was 10,280, at the four sites in Kisumu was 6,593, at the five sites in Rongo was 1,338, and at the 11 FACES-supported sites in Migori District is 4,882.

- b. Because there are not accurate data about the number of non-pregnant women of reproductive age at these sites, we applied estimates based on observations of client demographics at the FACES site in Kisumu, where 65% of all clients are adult females, 89% of the female population is of reproductive age, and 90% of the reproductive age females are not pregnant.
  - c. Applying these estimates, our eligible sample is approximately 12,023 women at 36 sites, an average of 333 women per site. For the sample size calculation, a conservative estimate of approximately 200 eligible women per site was used to allow for inclusion of smaller sites.
- 2. Effect size on primary outcome.

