## **EXPECTED APPLICATION OF RESULTS**

If integration of family planning services into HIV care and treatment appears feasible, acceptable, and effective at decreasing unintended pregnancies among HIV-infected women, the family planning intervention will be introduced into all FACES-supported PSC clinics. If the intervention does not appear to be feasible, acceptable, or effective based on the results of the trial, assessment of the integration will be conducted to try to identify ways in which the family planning intervention could be improved or changed. Modification of the intervention and reintroduction of it into HIV care and treatment will be considered based on trial results.

Ultimately, the findings of this research will help guide future research, policy, and interventions in the area of integrating family planning into HIV care. The ultimate goal is to create a feasible, acceptable, and effective family planning intervention that can be modified and applied elsewhere in Kenya and throughout Sub-Saharan Africa in order to increase access to effective contraception among HIV-infected women, thereby allowing them to make reproductive choices and to decrease unintended pregnancies.

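### The stated 80% power is supported for contraceptive prevalence only; for unintended pregnancy, the other primary outcome, no inputs are given and power is far lower under plausible assumptions

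*Protocol*

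**What the plan says.** Sample size considerations opens by saying that the ACLUSTER program was used to find the number of clusters "that we will need to assess changes in contraceptive prevalence and unintended pregnancy". Item 2a of the same section then says: "The primary outcome upon which we based our sample size calculation is contraceptive prevalence". The inputs that follow are a control prevalence of 22%, a target of 30%, two-sided alpha 0.05, power 0.8 and ICC 0.01. They lead to about 140 women at each of 18 sites (12 intervention, 6 control), 2,520 in all.

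The Data analysis plan begins its inferential paragraph with "Analysis of the primary outcomes, contraceptive prevalence and unintended pregnancy rates", specifies a weighted t-test between arms, and states: "These tests will be evaluated based on a two-sided alternative hypothesis, 80% power, and a 5% type I error rate".

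Expected application of results says that if integration appears feasible, acceptable and "effective at decreasing unintended pregnancies among HIV-infected women, the family planning intervention will be introduced into all FACES-supported PSC clinics". Contraceptive prevalence is not named in that section.

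**The concern.** Power has meaning only for a stated effect on a stated outcome. The protocol supplies these for contraceptive prevalence and for nothing else on the encounter-form data in women. No control rate, target reduction or ICC for unintended pregnancy appears anywhere, yet two sections read as if the trial were sized for it.

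The risk lies in interpretation. Suppose integration achieves its full 8-point rise in contraceptive use. The resulting fall in unintended pregnancy may still be well below what 18 sites can detect. A reader who takes the 80% at face value would treat a non-significant pregnancy comparison as informative evidence against the intervention, and the section on application of results makes that comparison matter.

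**Working it through.** **Method.** Compare 12 and 6 site-level proportions with m women per site.

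- Design effect: DE = 1 + (m − 1) × ICC.
- SE = √{DE × [p_c(1 − p_c)/(6m) + p_i(1 − p_i)/(12m)]}.
- Power is taken from the noncentral t distribution with 16 degrees of freedom and noncentrality (p_c − p_i)/SE, two-sided 5%.

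**Step 1: reproduce the plan's own figure.** With m = 140 and ICC 0.01, DE = 1 + 139 × 0.01 = 2.39. For 22% against 30%:

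SE = √{2.39 × [0.1716/840 + 0.2100/1680]} = 0.0281, and 0.08/0.0281 = 2.85.

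Power is 81% by the normal approximation and 76% with 16 degrees of freedom. The stated 80% for contraceptive prevalence is sound.

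**Step 2: what fall in unintended pregnancy goes with 22% to 30%?** The protocol does not say, so three assumptions are shown.

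- Unintended pregnancy proportional to non-use: 1 − 70/78 = 10.3%.
- Only a share w of women wish to avoid pregnancy, all users are among them, and methods are fully effective: relative fall = 0.08/(w − 0.22). With w = 0.6 this is 0.08/0.38 = 21%.
- The same with w = 0.5: 0.08/0.28 = 29%.

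The values of w are assumptions; no section of the protocol gives one.

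**Step 3: control risk.** No rate is given. Sample size considerations takes 90% of reproductive-age women at the Kisumu site as not pregnant, so about 10% pregnant. The Background cites over half of births in Kenya and Zambia as unintended. Together these suggest 5–10%, with 15% added as a favourable case. The 10% is a proportion pregnant at one time and not a nine-month incidence, so it is only a rough anchor.

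**Step 4: power for unintended pregnancies per woman, ICC 0.01.**

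| Women per site | Control risk | 10% fall | 21% fall | 29% fall | Fall detectable with 80% power |
|---|---|---|---|---|---|
| 140 | 5% | 6% | 11% | 17% | 74% |
| 140 | 10% | 8% | 18% | 30% | 53% |
| 140 | 15% | 10% | 26% | 44% | 43% |
| 333 | 5% | 7% | 13% | 21% | 66% |
| 333 | 10% | 9% | 22% | 38% | 47% |
| 333 | 15% | 11% | 32% | 54% | not calculated |

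One cell as an example: at 140 per site, 10% against 7.9% gives SE 0.0190, a ratio of 0.021/0.0190 = 1.11, and power 18%. The 333 rows use the average number of eligible women per site in Sample size considerations.

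**Step 5: how far must assumptions move to reach 80%?** The ICC has to be near zero. At 333 per site, ICC 0.001, 10% risk and a 29% fall, power is 84%; with the same ICC and 140 per site it is 55%. At 140 per site with ICC exactly 0, 15% risk and a 29% fall it only just reaches 80%.

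**The case against.** The best defence is that the protocol openly says which outcome drove the sample size, and that this calculation is right. Sizing on one of two primary outcomes is ordinary practice, and the sentence in the Data analysis plan can be taken as a loose list of test settings. This stands in part: there is no error of arithmetic. But the sentence directly follows the naming of both primary outcomes, and the opening of Sample size considerations also ties the number of sites to unintended pregnancy. As written, the claim covers an outcome for which there is no calculation.

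Second, the power figures rest on assumptions: the control risk, the share of women wishing to avoid pregnancy, and an ICC chosen in a calculation for another outcome. The protocol also expects benefit through more effective methods, better compliance and continuation, which the simple model leaves out. And 140 is the number required, while data are to come from all clients. All of this is fair. A reader might infer from the lower cells that power is capped at around 20%, or that the implied fall cannot exceed 21%. The documents support neither bound, as the 29% column and the 333 rows show.

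Third, a reader might infer that unintended pregnancy alone decides roll-out. It does not. Expected application of results sets no significance threshold, lists three conditions, and answers an unfavourable result with reassessment and possible modification and reintroduction. The design also foresees eventual integration at all 18 study sites.

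A reader might also extend the point to staff knowledge. The 50% against 60% target is stated for patients and no staff target is given, so that extension has no basis.

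**Conclusion.** The point holds as an unsupported power statement. The 80% applies to contraceptive prevalence in women and, on the protocol's inputs, to nothing else among the primary outcomes. At the protocol's ICC, with 5–10% control risk and relative falls of 10–29%, power for unintended pregnancy is about 6–30% at 140 women per site and 7–38% at 333, reaching about 54% at 15% risk. Detectable falls at 5–10% risk are about 53–74% and 47–66% respectively. These ranges are conditional on the stated assumptions, but no scenario examined at ICC 0.01 comes near 80%.

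The consequence is a possible misreading of a non-significant pregnancy result, not an automatic decision against integration. The sized comparison is unaffected. This should be fixed, and it does not put the main analysis in doubt.

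**What to change.** - **Data analysis plan:** confine the 80% power statement to contraceptive prevalence in women.
- **Sample size considerations:** remove unintended pregnancy from the stated purpose of the cluster calculation, or give its detectable difference with the assumed control rate and ICC.
- **Reporting:** present the pregnancy outcomes as estimates with confidence intervals.
- **Expected application of results:** keep the three conditions, and add that a non-significant pregnancy result will not by itself be read as lack of effect and will be interpreted together with contraceptive prevalence. Replacing the pregnancy criterion with contraceptive prevalence would change the programme's stated goal and is not needed to resolve this point.

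The cost is protocol wording only, with no added sites, clients or data. The one downside is that the stated power for the pregnancy outcome becomes less favourable.
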